## 3.3 Population

In Scotland our main population of interest is adults who have completed a full COVID-19 vaccination schedule (typically two doses) resident in the countries. Our secondary population of interest in Scotland is all adults.

In Brazil our primary population of interest is all adults who have received a booster dose, with primary series of any available vaccine.

For the test-negative design, in both countries, we will study all adults who have received a COVID-19 RT-PCR or Rapid Antigen^^[[1]](#footnote-0)^^ test after the begin of booster dose campaign in each country (Brazil: 2021/09/15; Scotland: 2021/09/15)

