**Table 2: Data items/variables and data sources in Brazil**

| **Data category** | **Data item** | **Data source** |
| --- | --- | --- |
| Sociodemographic | Sex | SI-PNI |
|  | Age | SI-PNI |
|  | Municipality-level IBP | SI-PNI |
|  | Education | (SIVEP-Gripe) |
|  | Race | SI-PNI, eSUS, SIVEP-Gripe |
|  | City |  |
| Clinical diagnoses | Underlying conditions  (Cardiac disease, chronic kidney disease, etc) | eSUS, SIVEP-Gripe |
| Vaccinations | Vaccine type | SI-PNI |
|  | Vaccine dose | SI-PNI |
|  | Vaccination date | SI-PNI |
|  | The primary reason for vaccination: 2 categories (comorbidities/other) | SI-PNI |
| Genomic Vigilance | Date of prevalence of variants | GISAID |
| Laboratory tests | Date of RT-PCR/rapid antigen test | eSUS |
|  | RT-PCR/rapid antigen positive SARS-CoV-2 | eSUS |
|  | RT-PCR/rapid antigen negative SARS-CoV-2 | eSUS |
| Secondary care  Mortality | COVID-19 hospital admission date | SIVEP-Gripe |
|  | COVID-19 death | SIVEP-Gripe/eSUS |
|  | COVID-19 death date | SIVEP-Gripe/eSUS |

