### 5.1.5 Analytical techniques

We will commence analysis by conducting descriptive analyses to visually inspect trends in vaccination delivery, age-specific COVID-19 hospitalisations and COVID-19 deaths, including by age group and sex. This will include checking the number of people who have received two doses and the length of follow-up available following the second dose by vaccine type. Including plotting Lexis diagram to afford for the correlated structure of the data (Calendar Time/Length of Follow-up)

For the analysis consisting of individuals with at least two doses, we will stratify the cohort based on the month of the second dose of each individual. The vaccination status will be classified as:

- Second dose:
  - <2 weeks
  - 2-9 weeks
  - 10-19 weeks
  - ≥20 weeks without a booster dose [Reference Period]
- Booster dose:
  - <2 week
  - 2-4 weeks
  - 5-8 weeks
  - 9-12 weeks
  - ≥13 weeks

This variable will be used to fit a Poisson regression to obtain rate ratios (RRs) and their 95% confidence intervals (CIs). If we observe overdispersion, we will consider using Negative Binomial regression models or Poisson with robust standard errors. Models will be adjusted for the relevant confounders above, including a set of dummy variables for calendar week.

The models will be fit to a dataset with all events and a random sample, without replacement, of 100 individuals per event (for hospitalisation and death, 10 for positive tests). The sample weights will be calculated to represent the sampling fraction, thus ensuring the correct calculation of the person-years at risk for the whole population.

The primary analysis for the test negative will be on individuals who are symptomatic at the time of test and the date of symptom onset is 0-10 days before the test. We will then establish the number of weeks post-vaccination for the cases and controls calculated as time between sample collection date and vaccine dose. The odds' ratio will be calculated using a logistic regression. Adjusted for: race/ethnicity, comorbidities, dummy variables for calendar week, age (five-year bands), sex. Controls will be defined based on a negative test.

We will also construct a propensity score to be tested among those in the primary cohort and use this as an inverse propensity weight.

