### 5.1.7 Sensitivity analysis

We will consider exploring the impact of alternative approaches to classifying the start of the exposed period (e.g. from day 7 after completion of the vaccination schedule), classifying COVID-19 hospitalisation based on primary diagnosis (rather than any diagnostic position), using only individuals with five days of fewer from symptom onset to test (reducing the risk of false-negative) and statistical adjustment for people with previous COVID-19 infection (rather than excluding them).

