# Appendix

## **Table S1. ICD-10 codes**

| **Code** | **Description** | **Category** |
| --- | --- | --- |
| U07.1 | COVID-19, virus identified | U07.1 |
| U07.2 | COVID-19, virus not identified | U07.2 |
| Source:<https://www.who.int/classifications/icd/COVID-19-coding-icd10.pdf> | | |

1. Rapid antigen test will be evaluated only in Brazil [↑](#footnote-ref-0)
2. Brazilian data will use only time between test and date of death, while Scotland will use ICD Codes and time between test and date of death and ICD-10 codes in the death record. [↑](#footnote-ref-1)
3. The first band is 7 years: 18-24, the last band is 90+ [↑](#footnote-ref-2)

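### The Brazilian test-negative analysis pools RT-PCR and rapid antigen results with no term, stratum or sensitivity analysis for test type, so the infection OR can be attenuated and, if test mix differs by booster status, shifted either way.

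*SAP*

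**What the plan says.** For the TND, SAP 3.3 states that "we will study all adults who have received a COVID-19 RT-PCR or Rapid Antigen" test, and footnote 1 to that sentence adds that "Rapid antigen test will be evaluated only in Brazil". Table 2 lists the Brazilian results as two combined items, "RT-PCR/rapid antigen positive SARS-CoV-2" and "RT-PCR/rapid antigen negative SARS-CoV-2". It has no separate item for test type.

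Section 5.1.5 sets the model: "The odds' ratio will be calculated using a logistic regression", followed by "Adjusted for: race/ethnicity, comorbidities, dummy variables for calendar week, age (five-year bands), sex. Controls will be defined based on a negative test". Test type is also absent from the Brazilian confounders (5.1.3), the stratifiers (5.1.4) and the sensitivity analyses (5.1.7).

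Three provisions bear on false negatives, none of them by test type:

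- Section 3.5 drops a negative test if a positive one follows within 7 days.
- Section 5.1.5 limits the primary TND to symptomatic people tested 0-10 days from onset.
- Section 5.1.7 offers, as something to be considered, "using only individuals with five days of fewer from symptom onset to test (reducing the risk of false-negative").

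Section 5.1.2 words the infection outcome as RT-PCR confirmed, which does not match 3.3 or Table 2.

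**The concern.** Pooling treats two tests as one. If antigen misses more infections, the chance that an infected person is counted as a control depends on which test was used. Two separate effects follow.

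1. **Attenuation.** Infected people among the controls pull the OR toward 1, even when test mix is the same in boosted and unboosted people.
2. **Mix shift.** If boosted and unboosted people receive the two tests in different proportions within the same week and covariate pattern, average sensitivity differs by exposure. The OR then moves even when the vaccine has no effect, and the direction depends on which group has more RT-PCR. The TND adjustment list has no geography or socioeconomic term, so a difference in mix by place would not be adjusted away.

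What is at stake is the Brazilian OR for Objective 2 and its comparison with Scotland, where antigen tests are not used. The SAP expects 10 million and 5 million boosted people in Brazil (3.6). A systematic shift of several percent may therefore be large beside the sampling error, and the confidence interval would not reveal it.

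**Working it through.** The SAP states no sensitivity, test mix, prevalence or expected OR for the TND, so there is no figure of its own to reproduce.

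**Assumptions (none from the SAP).** Sensitivity 0.95 for RT-PCR and 0.70 for antigen; perfect specificity; infection prevalence p0 = 0.20, 0.35 or 0.50 among unboosted people tested; test type independent of infection given booster status.

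**Formulas.** Let f be the RT-PCR share in a booster group (0 = unboosted, 1 = boosted).

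- Mean sensitivity: s = 0.95f + 0.70(1 - f)
- Boosted prevalence: odds(p1) = true OR × odds(p0)
- Observed OR = odds(p1·s1) / odds(p0·s0)

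**Equal mix, true OR 0.40.** For antigen only at p0 = 0.20, p1 = 0.0909, and the observed OR is odds(0.0636)/odds(0.140) = 0.0680/0.1628 = 0.417.

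| Test | p0 = 0.20 | p0 = 0.35 | p0 = 0.50 |
|---|---|---|---|
| RT-PCR only | 0.403 | 0.406 | 0.412 |
| Antigen only | 0.417 | 0.436 | 0.464 |

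**Unequal mix, true OR 1.** For shares of 30% (unboosted) and 50% (boosted), s0 = 0.775 and s1 = 0.825. At p0 = 0.20 the observed OR is odds(0.165)/odds(0.155) = 0.1976/0.1834 = 1.077.

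| RT-PCR share, unboosted / boosted | p0 = 0.20 | p0 = 0.35 | p0 = 0.50 |
|---|---|---|---|
| 30% / 35% | 1.019 | 1.022 | 1.027 |
| 30% / 40% | 1.038 | 1.045 | 1.054 |
| 30% / 50% | 1.077 | 1.091 | 1.110 |
| 50% / 30% | 0.928 | 0.917 | 0.901 |

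With shares of 30% and 50%, a true 0.40 reads 0.442, 0.460 and 0.487.

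**Second calculation, with fitted logistic models.** Expected counts were built with RT-PCR sensitivity 0.95 and specificity 0.999, antigen specificity 0.995, prevalence 0.40, and an antigen share of 50% in unboosted and 30-70% in boosted people. With no test-type term, a null OR reads:

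- 0.877-1.134 at antigen sensitivity 0.6
- 0.914-1.091 at 0.7
- 0.950-1.051 at 0.8
- 0.996-1.004 at 0.95, equal to RT-PCR, which shows that the difference in sensitivity drives the shift

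**Effect of a test-type term in the same models.** The null returns to 1.000 in every scenario. A true 0.50 at antigen sensitivity 0.7 reads 0.493-0.569 without the term and 0.523-0.533 with it. RT-PCR only gives about 0.509. The term removes the mix shift but leaves the attenuation; restricting to RT-PCR removes most of that.

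**The case against.** The strongest reply is that the plan already limits false negatives, that nothing in it shows a difference in test mix by booster status, and that the bias is small and conservative if the mix is equal. Much of this stands, and it rules out several stronger readings that a reader might infer.

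- **That onset time is the only safeguard against false negatives.** It is not. The 7-day rule in 3.5 also removes some, of either test type, but only among people who were retested and turned positive.
- **That any change in test mix shifts the OR.** Calendar-week dummies absorb the average change in positivity over time. The mix shift needs a difference by booster status within week and covariates. The SAP gives no evidence for or against one.
- **That a changing mix would be read as waning.** With equal mix within week the effect is small. A move from 50% to 70% antigen takes a true 0.40 from 0.410 to 0.413 at 20% prevalence, or from 0.439 to 0.450 at 50%.
- **That Objective 1 is biased to the same degree.** The calculation concerns infected people misplaced within one tested pool. Hospitalisation and death have their own definitions in 5.1.2, and nothing here sizes the effect on them.
- **That test type is already held as a variable.** Table 2 shows combined items only. The RT-PCR wording in 5.1.2 suggests the test can be identified, but that is an inference.

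The reply does not remove the omission. Section 5.1.5 fixes an adjustment list without test type, and no other section examines it. The 5-day analysis is optional and not split by test.

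**Conclusion.** The point holds for the Brazilian infection OR (Objective 2). As written, the model leaves antigen false negatives among the controls and cannot correct a difference in test mix by booster status. Under the stated assumptions the mix shift is about 2-3% on a null OR for a 5-point gap, 4-5% for 10 points and 8-11% for 20 points, with 0.90-0.93 for the reverse 20-point gap. Attenuation with equal mix is modest and toward the null. All of these sizes depend on sensitivities, prevalence and mix that the SAP does not give. The case for acting is that the remedy is cheap, not that a large bias has been shown. Whether antigen positives count as infection cases is also unsettled while 5.1.2 disagrees with 3.3 and Table 2; the figures above assume that they do.

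**What to change.** In 5.1.5, for Brazil:

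1. Include test type (RT-PCR or antigen) in the TND logistic model as a covariate or stratum. This removes the mix shift.
2. Report an RT-PCR-only OR by booster band beside the pooled OR, as a sensitivity analysis in 5.1.7. This limits antigen false negatives among the controls, which step 1 does not.
3. List test type as its own item in Table 2 after confirming that eSUS records it separately. If it does not, state this as a limitation.
4. Reconcile the RT-PCR wording of the infection outcome in 5.1.2 with 3.3 and Table 2, so that the same tests are named for cases and controls.

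The cost is SAP wording, one covariate if the field exists, and some loss of precision in the RT-PCR-only estimate.

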### 5.1.6 Corrections for multiple testing

Following previous epidemiological recommendations, we will not correct for multiple testing [3].

### 5.1.7 Sensitivity analysis

We will consider exploring the impact of alternative approaches to classifying the start of the exposed period (e.g. from day 7 after completion of the vaccination schedule), classifying COVID-19 hospitalisation based on primary diagnosis (rather than any diagnostic position), using only individuals with five days of fewer from symptom onset to test (reducing the risk of false-negative) and statistical adjustment for people with previous COVID-19 infection (rather than excluding them).

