## 3.5 Inclusion/exclusion criteria

Inclusion criteria for the primary cohort:

- Receive at least two doses of BNT162b2 or ChAdOx1 before or during the study period.

Exclusion criteria for the primary cohort:

- Inconsistent vaccination records (i.e. received a second dose with no record of a first dose, received doses from different vaccine types or interval between doses of less than 14 days)
- Missing essential covariates (sex, age, geography)
- Children (under the age of 18 years)
- Hospitalization previous to the study start date
- A positive test within 28 days of the study start date

Inclusion criteria for the TND:

- Receive at least two doses of BNT162b2 or ChAdOx1 at the sample collection date.

Exclusion criteria for the TND:

- Tests within 90 days of a previous positive test
- Negative tests followed by a positive test within 7 days
- Negative tests within 14 days of a previous negative test
- Missing essential covariates (sex, age, geography)
- Children (under the age of 18 years)

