## 4.2 Constructed variables

1. Previous infection, if an individual had a previous RT-PCR/Antigen positive test more than 90 days before the event of interest. Only the first positive test before the current event will be considered. This variable will be created differently for the cohort and TND.
   1. TND: Individuals with a previous RT-PCR or Antigen test positive considering the current sample collection date. (No previously infected, 91-180 days, >180 days)
   2. Cohort: Individuals with a previous RT-PCR or Antigen test considering the study start date (2021/09/15). (No previously infected,28-90 days,91-180 days, >180 days)
2. Interval between second and booster dose

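### Infections older than the 28-day (cohort) and 90-day (TND) windows are neither excluded nor in any stated adjustment list, although 5.1.7 presumes exclusion; the cohort variable is also anchored to one calendar date

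*SAP*

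**What the plan says.** Five sections of the SAP bear on previous infection.

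- **3.5, cohort.** The infection-related exclusion is "A positive test within 28 days of the study start date". A separate criterion removes "Hospitalization previous to the study start date", which concerns admissions and not infection as such.
- **3.5, test-negative design (TND).** The exclusion is "Tests within 90 days of a previous positive test".
- **4.2.** The lead sentence defines "Previous infection, if an individual had a previous RT-PCR/Antigen positive test more than 90 days before the event of interest" and adds "Only the first positive test before the current event will be considered". The TND version is set at sample collection, with levels for none, 91-180 days and more than 180 days. The cohort version is "Individuals with a previous RT-PCR or Antigen test considering the study start date (2021/09/15", with levels for none, 28-90, 91-180 and more than 180 days.
- **5.1.3 and 5.1.5.** Neither the general, the Scottish nor the Brazilian confounder list names previous infection. The cohort Poisson model refers back to those confounders and adds calendar week. The TND logistic model has its own list: "Adjusted for: race/ethnicity, comorbidities, dummy variables for calendar week, age (five-year bands), sex". The propensity score in 5.1.5 has no stated covariates.
- **5.1.7.** Among the alternatives that will be considered is "statistical adjustment for people with previous COVID-19 infection (rather than excluding them".

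**The concern.** The sections do not describe one primary analysis. Section 5.1.7 treats exclusion of previously infected people as the default, 3.5 and 4.2 keep most of them, and the stated models ignore the variable that 4.2 creates. An analyst could exclude, adjust for, or disregard older infection and find support in the SAP for each.

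This touches the main question. Boosted time bands are compared with people at least 20 weeks past their second dose without a booster, and waning is read from a trend over time since vaccination. Infection history plausibly affects both the outcome and whether or when someone takes a booster. If it differs between boosted and unboosted person-time, the RR or OR shifts. If that difference changes over follow-up, part of the shift can look like waning.

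The cohort has a second difficulty. It is open and admits people who complete two doses during the study period, yet infection history and the 28-day exclusion are both read at a single date.

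**Working it through.** **Step 1: is exclusion the primary rule?** If 3.5 excluded everyone with a previous infection, the infected levels in 4.2 would be empty. They are not: the cohort has three (28-90, 91-180, more than 180 days) and the TND two (91-180, more than 180 days). Their lower limits match the 28-day and 90-day windows in 3.5. So 3.5 and 4.2 agree that older infections stay in, and 5.1.7 is the section out of line.

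**Step 2: is the variable in a primary model?** It is absent from all three lists in 5.1.3, hence from the Poisson model that points to them, and from the TND list in 5.1.5. Adjustment for it is named only in 5.1.7, as an option.

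**Step 3: at what date is it classified?** The lead sentence of 4.2 counts back from the event of interest. The cohort sub-item counts back from 15 September 2021 and has a 28-90 day level that the lead sentence's 90-day limit would not allow. Someone who completes two doses after 15 September and tests positive between that date and entry is classed as not previously infected, and the 28-day rule is not applied at their entry. No updating or censoring at later infection is stated.

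**Step 4: how large could the effect be?** The SAP has no figure to reproduce, so every input here is an assumption. For an omitted binary confounder,

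factor on RR = [1 - p1 × e] / [1 - p0 × e],

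where p1 and p0 are the previously infected shares of boosted and reference person-time, and e is the protection that previous infection gives against the severe outcome.

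| e | p1 | p0 | Factor | True RR 0.30 reads |
|---|---|---|---|---|
| 0.8 | 0.15 | 0.20 | 0.88/0.84 = 1.05 | 0.31 |
| 0.8 | 0.15 | 0.30 | 0.88/0.76 = 1.16 | 0.35 |
| 0.8 | 0.15 | 0.40 | 0.88/0.68 = 1.29 | 0.39 |
| 0.5 | 0.15 | 0.20 | 0.925/0.90 = 1.03 | 0.31 |
| 0.5 | 0.15 | 0.30 | 0.925/0.85 = 1.09 | 0.33 |
| 0.5 | 0.15 | 0.40 | 0.925/0.80 = 1.16 | 0.35 |
| any | equal to p0 | | 1.00 | 0.30 |

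A second set, with protection of 0.5 to 0.9 and shares from 5% against 10% up to 10% against 30%, gives 1.03 to 1.25. If the shares move from the first pair to the second during follow-up, the crude late-to-early ratio is 1.118/1.026 = 1.09 at e = 0.5 and 1.247/1.049 = 1.19 at e = 0.9. If infection were commoner among the boosted, the factors would fall below 1.

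**The case against.** The best defence is that the SAP does deal with infection. Recent positives are excluded in both designs, and people hospitalised before study start are removed from the cohort. The words in 5.1.7 could refer to those windows only. The 5.1.3 lists are worded as intentions, the variable in 4.2 has no other evident purpose, and the propensity score might include it. On this view a list item was forgotten.

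Part of this stands. A reader might infer that previous infection is ignored altogether; the exclusions in 3.5 show otherwise, and the gap is older infection. The cohort date also looks more like an inconsistency within 4.2 than a settled decision, and the TND variable is not affected by it. But an intention to adjust is not a specification, the TND list reads as closed, and a propensity score without covariates cannot fill the gap.

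The bias argument also has limits:

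- The SAP gives no data on infection by booster status, so neither direction nor size is established.
- The arithmetic is a crude two-group ratio. The plan stratifies by month of second dose and uses calendar-week dummies. When people boosted at different times are compared within the same week, they share the same unboosted reference, and its contamination cancels between bands. Some bias may remain through comparisons across weeks, but the factors in the table cannot be carried straight into the trend test.
- The calculation concerns an RR for severe outcomes and does not size the TND odds ratio for infection.
- The first positive before an event can mean the earliest or the nearest looking back. Only the former would place a recent reinfection in the oldest category, so this wording needs clarifying but is not a demonstrated error.

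**Conclusion.** The point holds. Section 5.1.7 presumes an exclusion that 3.5 does not contain, and a confounder the SAP has already constructed is in no stated primary model. Followed as written, the Poisson and logistic models leave older infection unadjusted, and it can confound the booster estimates and their apparent waning. The illustrative factor on the RR is about 1.03 to 1.29 under the assumed shares and protection, and 1.00 with equal shares. In the cohort, the reference date fits neither the open design nor the lead sentence of 4.2.

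A reader might go further and infer that the omission will produce false waning. The SAP does not support that, since it depends on infection differences that it does not report. A reader might also infer that the primary cohort model must use time-updated infection. That does not follow either: infection after a booster may be affected by the booster and is itself a secondary outcome, so adjusting for it can condition on an intermediate and change what is estimated.

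**What to change.** Before the analysis, make 3.5, 4.2, 5.1.3, 5.1.5 and 5.1.7 agree:

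1. Add the 4.2 previous-infection variable to the adjustment set of the primary cohort Poisson model and of the TND logistic model.
2. In the cohort, classify it and apply the 28-day exclusion at each person's cohort entry. For those who already had two doses on 15 September 2021, that is the same date as now.
3. State in 4.2 that the most recent positive test before the reference date is used, and bring the lead sentence into line with the cohort levels.
4. Reverse 5.1.7, so that excluding previously infected people becomes the sensitivity analysis.
5. Optionally, add a sensitivity analysis with time-updated infection, or with censoring at infection during follow-up, noting that post-booster infection may be an intermediate.

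The cost is small. Test results and dates are already among the data items in Tables 1 and 2, so items 1 to 4 need only revised wording and one variable reclassified at entry. Item 5 adds a further split of person-time, or a censoring date.
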